### 12 Lead Electrocardiogram^20

A standard 12 lead ECG will be recorded at the screening and at the end of the study as per the methodology approved by the British Cardiovascular Society for recording a standard 12 lead electrocardiogram. Both absolute QT interval and corrected QT interval will be noted from precordial leads and Lead II. QT interval will be corrected using Fridericia's formula ( $QT_c = QT/RR^{0.33}$  i.e. Observed QT interval divided by cube root of RR interval, in seconds).

### Overall tolerability evaluation:

The overall tolerability to study medication will be evaluated at the end of study as per the following criteria:

| Grade     | Description                                                                                                                       |
|-----------|-----------------------------------------------------------------------------------------------------------------------------------|
| Excellent | No adverse event                                                                                                                  |
| Good      | Mild adverse event(s) reported which subsided with or without medication and did not necessitate stoppage of study medication     |
| Fair      | Moderate adverse event(s) reported which subsided with or without medication and did not necessitate stoppage of study medication |
| Poor      | Severe or serious adverse event(s) which necessitated stoppage of study medication                                                |

The safety endpoints would be:

- Local and systemic adverse events reported during the study
- Serious adverse events reported during the study
- Overall tolerability evaluation at the end of study

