### 10.2.2 Adverse Events Recording

Adverse events will be elicited using the open question - Have you noticed any change in your health since your last visit? Events involving adverse drug reactions, illnesses with onset during the study or exacerbation of pre-existing illnesses should be recorded.

All observed or volunteered adverse events regardless of treatment group or suspected causal relationship to the study test products will be recorded on the adverse event page of the CRF. Safety data including adverse events will be tabulated for clinical review.

For all adverse events, the Investigator must pursue and obtain information adequate both to determine the outcome of the adverse event and to assess whether it meets the criteria for classification of a serious adverse event requiring immediate notification to the Sponsor's representative / medical expert.

Follow-up of the adverse event, even after the date of therapy discontinuation, is required if the adverse event or its sequel persist. Follow-up is required until the event or its sequel resolve or stabilises at a level acceptable to the Investigator and the study monitor.

|                                                                                  |                                                                                                       |                                                              |
|----------------------------------------------------------------------------------|-------------------------------------------------------------------------------------------------------|--------------------------------------------------------------|
| [figure not shown] | Clinical trial to evaluate efficacy and safety of Amla Extract (AMX160) in patients with Dyslipidemia | Project No. AN-03ASE
0115H2-SYN02
Ver.01, Dt: 01-01-15 |
|----------------------------------------------------------------------------------|-------------------------------------------------------------------------------------------------------|--------------------------------------------------------------|

All the adverse events will be documented in the respective CRFs including

1. Type of adverse event
2. Date of onset
3. Severity
4. Treatment given
5. Association or relationship to the study medication
6. Date of resolution
7. Duration
8. Outcome
9. Whether the adverse event is serious or not

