|----------------------------------------------------------------------------------|-------------------------------------------------------------------------------------------------------|--------------------------------------------------------------|

|                                         |                                                                                                                                                                                                         |
|-----------------------------------------|---------------------------------------------------------------------------------------------------------------------------------------------------------------------------------------------------------|
| Conditional/
Unclassified    | 
 
• Event or laboratory test abnormality More data for proper assessment needed, or
 
• Additional data under examination
 
                        |
| Unassessable/
Unclassifiable | 
 
• Report suggesting an adverse reaction Cannot be judged because information is insufficient or contradictory Data cannot be supplemented or verified
 
 |

\* All points should be reasonably complied with

The assessment of intensity/severity will be determined based on the investigator's clinical judgment using the following definitions:

Mild: An event that is easily tolerated by the patient, causing minimal discomfort and not interfering with everyday activities.

Moderate: An event that is sufficiently discomforting to interfere with normal everyday activities.

Severe: An event that prevents normal everyday activities.

Note: severity is not the same as 'seriousness', which is defined in SAE above

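### The overall tolerability scale, a named safety endpoint, is not exhaustive: read literally, 12 of 24 event profiles have no grade

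*Protocol*

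**What the plan says.** Protocol section 7.2 lists three safety endpoints, and the third is "Overall tolerability evaluation at the end of study". The scale has four grades. The best, Excellent, is for patients who had no event at all. For the next, Good, the protocol asks for "Mild adverse event(s) reported which subsided with or without medication and did not necessitate stoppage of study medication". The third grade, Fair, sets the same conditions for events of moderate severity. The lowest, Poor, is reserved for "Severe or serious adverse event(s) which necessitated stoppage of study medication".

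The Overall Tolerability Evaluation form in the appendices prints the same four grades as tick boxes. Neither place offers a box for other cases, a rule for an event that meets no description, or a rule for choosing between grades when more than one event has occurred.

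**The concern.** Good and Fair each set three conditions at once: a severity, resolution, and no stoppage. Poor sets two: severe or serious, and stoppage. Severity, seriousness, resolution and stoppage can vary separately, so a scale built this way may leave gaps between its grades.

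The rest of the protocol shows that they do vary separately. Under section 10.2.2, severity is judged by the effect on daily life: "Severe: An event that prevents normal everyday activities". Stopping plays no part in that definition. The note below it adds that "severity is not the same as 'seriousness', which is defined in SAE above". Section 10.2.2 also foresees events that outlast treatment: "Follow-up of the adverse event, even after the date of therapy discontinuation, is required if the adverse event or its sequel persist". Section 6.3 lets a patient withdraw consent, or the investigator withdraw a patient, with no severity threshold, so a mild or moderate event can lead to stopping. The text on discontinuation asks for the final evaluation when the product is stopped, or soon after, so patients who stop early should reach this form.

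At stake is whether the endpoint can be completed the same way at every centre. For a profile that matches no grade, an investigator has no rule to follow. Leaving the form blank and ticking a neighbouring grade are both plausible responses, and sites may differ in which they choose.

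**Working it through.** No figure in the protocol needs reproducing. The check is a full enumeration against the literal wording.

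**Inputs**

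- Grade descriptions: section 7.2 and the appendix form.
- Severity: mild, moderate or severe (section 10.2.2).
- Seriousness: yes or no (section 10.2.2).
- Stoppage of study medication: yes or no (grade descriptions).
- Subsided: yes or no (grade descriptions).

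**Number of profiles:** 3 × 2 × 2 × 2 = 24.

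**Rules applied**

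- Good: mild, subsided, not stopped.
- Fair: moderate, subsided, not stopped.
- Poor: (severe or serious) and stopped, whatever the resolution.

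| Severity | Serious | Stopped, subsided | Stopped, not subsided | Not stopped, subsided | Not stopped, not subsided |
|---|---|---|---|---|---|
| Mild | no | none | none | Good | none |
| Mild | yes | Poor | Poor | Good | none |
| Moderate | no | none | none | Fair | none |
| Moderate | yes | Poor | Poor | Fair | none |
| Severe | no | Poor | Poor | none | none |
| Severe | yes | Poor | Poor | none | none |

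**Graded:** Good 2 + Fair 2 + Poor 8 = 12.

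**Ungraded:**

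- severe, not stopped: 2 (serious or not) × 2 (subsided or not) = 4;
- non-serious mild or moderate, stopped: 2 (severities) × 2 (subsided or not) = 4;
- mild or moderate, not subsided, not stopped: 2 (severities) × 2 (serious or not) = 4;
- total: 4 + 4 + 4 = 12 of 24.

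**By seriousness:** among non-serious events 2 + 4 + 2 = 8 of 12 are ungraded. Among serious events 2 + 0 + 2 = 4 of 12 are ungraded.

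**Sensitivity to wording:** the stoppage clause in Poor could be taken to qualify only serious events. Every severe event is then Poor, the first group of 4 disappears, and 12 − 4 = 8 of 24 remain ungraded.

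**A related misplacement:** two profiles do receive a grade, but an odd one. A serious event of mild severity that subsided without stoppage is Good, and the same event at moderate severity is Fair.

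**The case against.** The strongest reply is that little depends on this scale. It is the third of three safety endpoints, and adverse events and serious adverse events are the other two. Section 10.2.2 records severity, seriousness, treatment, causality and outcome for every event, and the reason for discontinuation goes in the CRF. A patient without a grade loses a summary label, not safety data. The primary endpoint and the sample size are untouched. Section 10.1 says that earlier dyslipidaemia studies of the product reported no adverse events, so few such cases may arise. All of this stands, and it limits the weight of the point. It does not close the gap. Section 10.1 itself lists abdominal pain, nausea, fever and vomiting as possible. The grade is ticked by the investigator from fixed wording, so this is not a detail deferred to an analysis plan.

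The table also tempts a reader to infer more than it supports:

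- That every unresolved event is ungradable. Unresolved severe or serious events that led to stoppage are Poor.
- That every mild or moderate event leading to stoppage is ungradable. If such an event is serious, it is Poor.
- That every serious event managed without stoppage lacks a grade. If it is mild or moderate and subsided, it is Good or Fair.
- That two thirds of cases fail. The 8 of 12 applies to non-serious profiles only; the full count is 12 of 24.
- That these fractions describe patients. They count combinations of attributes, and the document gives no event rates.

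**Conclusion.** The point holds as a minor finding. Taken literally, the scale gives no grade to 12 of 24 event profiles, or to 8 of 24 on the more lenient reading of Poor. It also lets two serious-event profiles be graded Good or Fair. The sections cited show that the ungraded profiles can occur, and nothing else in the protocol assigns them a grade.

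The effect is confined to this one summary endpoint. How many of the 98 patients would be affected cannot be derived. For scale only, one patient in an arm of 49 is 1/49, about 2% of that arm. The count rests on reading each grade description as written and on treating severity, seriousness, stoppage and resolution as separate attributes. The first three are separate by the protocol's own definitions, and resolution is recorded as its own item.

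**What to change.** In section 7.2 and on the form, make the grades exhaustive and mutually exclusive, and state that the worst applicable grade is assigned. For example:

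- Excellent: no adverse event.
- Good: worst event mild, none serious, none leading to stoppage.
- Fair: worst event moderate, none serious, none leading to stoppage.
- Poor: any severe or serious event, or any event that led to stoppage.

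Resolution leaves the grade and is taken from the outcome already recorded on the adverse event page. Against the same 24 profiles this gives Good 2, Fair 2 and Poor 20 (severe 8, serious mild or moderate 8, non-serious mild or moderate with stoppage 4). The total is 24, with no gap and no overlap. Excluding serious events from Good and Fair is necessary; otherwise a serious mild or moderate event without stoppage would meet two grades.

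The downside is that a non-serious mild event that led to stoppage shares Poor with severe events. To keep that visible, also report adverse event severity and discontinuations due to adverse events by arm. Other placements are possible, provided each profile has exactly one grade.

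The cost is an edit to one table and one form. Severity, seriousness and outcome come from the adverse event page, and stoppage comes from the discontinuation reason in the CRF, so no further data collection is needed.

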### **7.3 Laboratory Investigations**

A Central Clinical Pathology Laboratory will be used for all laboratory investigations. Methods to be used for the laboratory tests are specific to the Laboratory. Lab investigations to be conducted are; Haematological parameters include haemoglobin levels, total leucocyte count, Absolute Neutrophil Count (ANC), platelet count. Biochemical parameters include fasting blood sugar, blood urea, serum creatinine, serum bilirubin, SGOT, SGPT, TG, TC, LDL, HDL, VLDL, Apo A1, Apo B, hs-CRP, Homocysteine, HbA1C, TSH, CoQ10 and HMG Coenzyme Reductase activity. Serum pregnancy test will be done during screening and end of study in females of child bearing potential.

|                                                                                  |                                                                                                       |                                                              |
|----------------------------------------------------------------------------------|-------------------------------------------------------------------------------------------------------|--------------------------------------------------------------|
| [figure not shown] | Clinical trial to evaluate efficacy and safety of Amla Extract (AMX160) in patients with Dyslipidemia | Project No. AN-03ASE
0115H2-SYN02
Ver.01, Dt: 01-01-15 |
|----------------------------------------------------------------------------------|-------------------------------------------------------------------------------------------------------|--------------------------------------------------------------|

The schedule for laboratory test is shown in table below:

| Parameter                                                                                                     | Visit 1
Screening | Visit 2
(Day 0)* | Visit 3
(Week 4) | Visit 4
(Week 8) | Visit 5
(Week 12) |
|---------------------------------------------------------------------------------------------------------------|----------------------|---------------------|---------------------|---------------------|----------------------|
| Efficacy                                                                                               |                      |                     |                     |                     |                      |
| TG                                                                                                     | √                    |                     | √                   | √                   | √                    |
| LDL                                                                                                    | √                    |                     | √                   | √                   | √                    |
| HDL                                                                                                    | √                    |                     | √                   | √                   | √                    |
| VLDL                                                                                                   | √                    |                     | √                   | √                   | √                    |
| TC                                                                                                     | √                    |                     | √                   | √                   | √                    |
| Apo A1                                                                                                 |                      | √                   |                     |                     | √                    |
| Apo B                                                                                                  |                      | √                   |                     |                     | √                    |
| hs CRP                                                                                                 |                      | √                   |                     |                     | √                    |
| Homocysteine                                                                                           |                      | √                   |                     |                     | √                    |
| FPG                                                                                                    | √                    |                     | √                   | √                   | √                    |
| CoQ10                                                                                                  |                      | √                   |                     |                     | √                    |
| HbA1c                                                                                                  |                      | √                   |                     |                     | √                    |
| HMG Coenzyme
Reductase activity                                                                    |                      | √                   |                     |                     | √                    |
| Safety                                                                                                 |                      |                     |                     |                     |                      |
| CBC                                                                                                    | √                    |                     |                     |                     | √                    |
| LFT (SGOT, SGPT,
bilirubin)                                                                        | √                    |                     |                     |                     | √                    |
| RFT (Urea, creatinine)                                                                                 | √                    |                     |                     |                     | √                    |
| TSH                                                                                                    |                      | √                   |                     |                     | √                    |
| SPT                                                                                                    | √                    |                     |                     |                     | √                    |
| Urine (R/M)                                                                                            | √                    |                     |                     |                     | √                    |
| ECG                                                                                                    | √                    |                     |                     |                     | √                    |
| * Blood sample will not be collected; analysis to be carried out using blood collected during screening visit |                      |                     |                     |                     |                      |

## 8 Study Conduct

The patients fulfilling the inclusion and exclusion criteria will be enrolled in the trial and will be randomized to receive either of the study medications in a double blinded

|                                                                                  |                                                                                                       |                                                              |
|----------------------------------------------------------------------------------|-------------------------------------------------------------------------------------------------------|--------------------------------------------------------------|
| [figure not shown] | Clinical trial to evaluate efficacy and safety of Amla Extract (AMX160) in patients with Dyslipidemia | Project No. AN-03ASE
0115H2-SYN02
Ver.01, Dt: 01-01-15 |
|----------------------------------------------------------------------------------|-------------------------------------------------------------------------------------------------------|--------------------------------------------------------------|

manner. The patients will be followed on an outpatient basis as per the schedule of visits mentioned below. Though every effort will be made to adhere to the schedule of visits, a window period of  $\pm 5$  days for will be permitted. Further, on all the scheduled visits the following assessments will be done and recorded in the CRF.

#### Activity Chart

| Activity                                | Visit 1
(Day -7) | Visit 2
(Day 0) | Visit 3
(Day 28 $\pm$
5 days) | Visit 4
(Day 56
$\pm$ 5 days) | Visit 5
(Day 84
$\pm$ 5 days) |
|-----------------------------------------|---------------------|--------------------|-------------------------------------|-------------------------------------|-------------------------------------|
| Informed Consent                        | √                   |                    |                                     |                                     |                                     |
| Demographics &
Medical History       | √                   |                    |                                     |                                     |                                     |
| Inclusion / Exclusion
criteria check | √                   | √                  |                                     |                                     |                                     |
| ECG                                     | √                   |                    |                                     |                                     | √                                   |
| Lab investigations                      | √                   | √*                 | √                                   | √                                   | √                                   |
| Vital Signs &
Clinical Examination   | √                   | √                  | √                                   | √                                   | √                                   |
| Dispensing of Study
Medication       |                     | √                  | √                                   | √                                   |                                     |
| Study Medication
Count               |                     |                    | √                                   | √                                   | √                                   |
| Recording of
Adverse Events          |                     |                    | √                                   | √                                   | √                                   |
| Concomitant Disease
and Medications  | √                   | √                  | √                                   | √                                   | √                                   |
| Overall Assessment
of Tolerability   |                     |                    |                                     |                                     | √                                   |
| Study Completion                        |                     |                    |                                     |                                     | √                                   |

\*No blood collection. Use blood sample collected on screening visit

